## Exclusion criteria for enrollment

The following criteria will be checked at the time of study entry. If any apply at the time of study entry, the subject must not be included in the study:

- Prior receipt of any investigational malaria vaccine
- Prior receipt of a vaccine containing either QS-21, MPL or AS02A or AS01B
- Use of any investigational or non-registered drug or vaccine other than the study vaccine within 30 days preceding the first dose of study vaccine, or planned use during the study period
- Administration of chronic (defined as more than 14 days) immunosuppressants or other immune modifying drugs within six months of vaccination. For corticosteroids, this is defined as prednisone, or equivalent, 0.5 mg/kg/day. Inhaled and topical steroids are allowed.
- Planned administration of a vaccine not foreseen by the study protocol within 30 days of the first dose of the study vaccine.
- Any confirmed or suspected immunosuppressive or immunodeficient condition, including human immunodeficiency virus (HIV) infection
- A family history of congenital or hereditary immunodeficiency
- Chronic or active neurologic disease including seizure disorder
- History of splenectomy
- Acute or chronic, clinically significant pulmonary, cardiovascular, hepatic or renal functional abnormality, as determined by physical examination or abnormal baseline laboratory screening tests
  - ALT above normal range Table 8
  - Creatinine above normal range as defined in Table 8
  - Hemoglobin below normal range as defined in Table 9
  - Platelet count below normal range as defined in Table 9
  - Total white cell count below normal range as defined in Table 9
- Acute disease at the time of enrollment (acute disease is defined as the presence of a moderate or severe illness with or without fever). All vaccines can be administered to persons with a minor illness, such as diarrhea or mild upper respiratory infection without fever, i.e. Oral temperature < 37.5°C.
- Hepatomegaly, right upper quadrant abdominal pain or tenderness
- Administration of immunoglobulins and/or any blood products within the three months preceding the first dose of study vaccine or planned administration during the study period
- Pregnant or lactating female
- Suspected or known current alcohol abuse/drug abuse as obtained by history and physical examination
- Female who is willing or intends to become pregnant during the study
- Any history of allergic reaction or anaphylaxis to previous vaccination
- Unwilling to allow blood samples to be stored for future use
- Inability to make follow up visits
- Allergy to kanamycin, nickel, or imidazole
- Any other significant finding that in the opinion of the investigator would increase the risk of having an adverse outcome from participating in this study
- Previous allergy to Rabies Vaccine
- Allergy to chicken and chicken products

## Elimination criteria during the study

The following criteria should be checked at each visit subsequent to the first vaccination

- Use of any investigational or non-registered product (drug or vaccine) other than the study vaccine(s) during the study period.
- Administration of chronic (defined as more than 14 days) immunosuppressants or other immune modifying drugs within six months of vaccination. For corticosteroids, this is defined as prednisone, or equivalent,  0.5 mg/kg/day. Inhaled and topical steroids are allowed.
- Administration of immunoglobulins and/or any blood products during the study period
- Clinical evidence of drug abuse, intoxication during follow-up visits, or other medical condition that would increase the risk of an adverse event or possible harm to the volunteer from further participation in this study.
- Poor Reliability/Keeping Appointments
- Any other concern of the PI or other investigator that precludes volunteer involvement in the study

### Contraindications to vaccination

**Absolute contraindications to further vaccination**

The following adverse events (AEs) constitute absolute contraindications to further administration of FMP010/AS01B or rabies vaccine Rabipur®; if any of these AEs occur during the study, the subject must not receive additional doses of vaccine but may continue other study procedures at the discretion of the investigator. The subject must be followed until resolution of the event, as with any AE.

- Acute allergic reaction, significant IgE-mediated event or anaphylactic shock following the administration of vaccine investigational product;
- Pregnancy, i.e. a positive urine test.

**Indications for deferral of vaccination**

The following AEs constitute contraindications to administration of FMP010/AS01B or rabies vaccine, Rabipur, at that point in time. If any one of these AEs occurs at the time scheduled for administration of investigational product, the investigational product may be administered to the subject at a later date but within the time window specified in the protocol or withdrawn at the discretion of the investigator. The subject must be followed until resolution of the event, as with any AE.

- Acute disease at the time of administration of investigational product (acute disease is defined as the presence of a moderate or severe illness with or without fever). All vaccines can be administered to persons with a minor illness such as diarrhea or mild upper respiratory infection without fever, i.e. Oral temperature <37.5°C
- Oral temperature of 37.5°C

# CONDUCT OF STUDY

## Principal Investigators and Monitors

[name] and [name] are the investigators for USAMRU-K Phase (Part B) of this study and are responsible for the conduct of the protocol, the actions of all other investigators, the safety of the volunteers, and all documentation and reporting. The PI is also responsible for training and maintaining all training files for all staff.

Associate investigators will be involved in screening of patients, recording of solicited and unsolicited symptoms, and initial evaluation of adverse events. All investigators who will review the subjects will have a copy of their medical license in the study file at the Regulatory Affairs Office.

[name] is the medical monitor from Kenya assigned to this study. He is a qualified physician not associated with this protocol who is able to monitor the volunteers during the conduct of the study and ensure that adequate medical care is provided for conditions that may arise during the study. He will review all SAEs (per ICH definitions) associated with the protocol and provide an unbiased written report of the event within 10 calendar days of the initial report. At a minimum, the medical monitor will comment on the outcomes of SAE and relationship of the SAE to the test article. The medical monitor will also indicate whether he/she concurs with the details of the report provided by the study investigator.

## 5.2 Ethics and regulatory considerations

The study will be conducted IAW ICH GCP, the Common Rule 32 CFR 219, applicable Kenyan guidelines; and OTSG and HSSRB regulations and policies

### Institutional Review Board/Independent Ethics Committee (IRB/IEC)

The IRBs must be constituted according to the local laws/customs of each participating country. For all trials conducted under the regulatory authority of the US FDA and under this IND application, it is required that the approving IRB/IEC be duly constituted and function IAW 21 CFR 56.

### Informed consent

- Informed consent will be obtained IAW 21 CFR 50.25 and the principles of the 1996 version of the Declaration of Helsinki.
- Information will be given in both oral and written form whenever possible and deemed appropriate by the IRB. The written consent document will embody the required and all applicable optional elements of informed consent as described in 21 CFR 50.25 and the 1996 version of the Declaration of Helsinki. In addition, the consent document will adhere to the ICH Harmonized Tripartite Guideline for GCP (E6) and will comply with DoD policy and regulations. An investigator or designate will describe the protocol to potential subjects. The Subject Information and Consent Form may be read to the subjects, but, in any event, the investigator or designate shall give the subjects ample opportunity to inquire about details of the study and ask any questions before dating and signing the Consent Form. Subject information and consent forms must be in a language fully comprehensible to the prospective subjects. All illiterate individuals will have the study, the Subject Information and Consent Form explained to them point by point by the interviewer in the presence of an impartial witness.
- Each subject’s signed informed consent form must be kept on file by the investigator for possible inspection by Regulatory Authorities and/or GSK Biologicals’ professional and Regulatory Compliance persons. The subjects should receive a copy of the signed and dated written informed consent form and any other written information provided to the subjects.

**Audits and Inspections**

Knowledge of any pending compliance inspections/visit by the FDA, OHRP, or other government agency concerning clinical investigation or research, the issuance of Inspection Reports, FDA Form 483, warning letters or actions taken by any Regulatory Agencies including legal or medical actions and any instances of serious or continuing noncompliance with the regulations or requirements will be reported immediately to the KEMRI ERC and WRAIR IRB. WRAIR IRB will report to USAMRMC ORP/HRPO as per SOP UWZ-C-636.

## 5.3 General Study Aspects

The community in which the study will take place will be informed about the nature and design of the study. Community leaders (assistant chiefs and local village elders) will be formally briefed in their own language on the nature and purpose of the study. They, in addition to the study volunteers, will have the opportunity to ask questions of the Investigator or his designees.

Adults aged 18 to 50 years will be recruited from the villages around Kisumu West District. Non-coercive means of recruitment will be used according to existing U.S. Army regulations (viz., AR 70-25 and AR 40-38). It is estimated based on previous clinical trial experience at Kisumu West District that approximately five times the number of volunteers to be enrolled will need to be screened in order to reach the target number of 30; therefore approximately 150 volunteers will be screened. Prospective subjects will view a videotaped briefing on the nature and purpose of the study and will then receive both oral and written explanations of the study. Afterwards, written informed consent will be obtained from each person who wants to participate in the study. No question relating to the potential study subjects health will be asked prior to consenting. To verify age, study staff will check national ID card or birth certificates, or letter from chief/elder of the village. So that language and illiteracy will not be impediments to informed consent, all briefings and explanations will be in the local language.

### Screening

Volunteers with a written Informed Consent, signed/thumb printed and dated will be eligible to be screened for Part B of the trial. Screening evaluation will include:

- a medical history through a one-on-one interview with a clinician.
- physical examination
- laboratory tests, which include complete blood count (CBC) using ACT 5 Diff or its equivalent.
- Serum glucose, creatinine, AST, ALT, alkaline phosphatase, total Bilirubin using the Selectra E Autoanlyzer or its equivalent.
- HIV as below described
- genotype for Sickle Cell and G6PD status using Biorad Analyzer or its equivalent.
- Alpha Thalassaemia
- Urine -HCG will be obtained on all female volunteers and serum β-HCG for confirmation where necessary.
- Volunteers may be screened more than once if re-screening is determined to be necessary (e.g. after treatment for malaria).

Volunteers will be excluded from participation if they have any of the exclusion criteria indicated in section 4.4 above or have any other finding that would increase the risk of having an adverse outcome during the conduct of the trial. The reason for exclusion will be discussed with the volunteer.

For HIV, rapid tests will be used for screening. (Determine and Unigold) will be used to carry out the test. Western blot will be done as the confirmatory test for those with indeterminate results. . Volunteers found to be seropositive for HIV will be counseled by a member of the study staff and referred to a HIV care center for further evaluation.

All screening tests will be completed within 60 days prior to entry into the study. Information gathered during screening (medical history, physical examination, and laboratory analysis) will be recorded in the Source Documents and, for enrolled volunteers, also on the case report forms (CRFs).

A photograph will be taken of each volunteer who is screened and stored securely in a computer at the CTC. When screening and review of inclusion/exclusion criteria are complete, a picture ID card of each eligible volunteer will be created using the stored photo. The ID card will include the subject’s name, photo, subject number, study number, study name, and contact information for the CTC. This will ensure that the subject can contact an investigator and/or the CTC. Copies of these pictures will be kept in the subjects records to aid the study staff in confirmation of the volunteers’ identification for future visits. The photos of subjects who are determined ineligible to participate will be deleted from the computer.

At the screening visit each subject will be given a Screening Number and a screening record will be initiated. Volunteer Study Numbers will be issued at randomization for the first vaccination. They will be issued consecutively in the order in which the subjects arrive at the clinical trials center. This Study Number will be used throughout the study to identify every document and blood sample associated with the volunteer.

Screening records will be converted to Study Records if the volunteer is randomized at the first vaccination visit. The Study Record will contain the Volunteer’s Study Number, date of birth, demographics, screening results, and all study information.

Clinical lab tests will be performed by the WRP lab or coordinated with a local reference lab.

### Study Design

This trial will be conducted in two parts. Part A will be conducted in the US at WRAIR and Part B in at the Walter Reed Project/KEMRI in Kisumu, Kenya. A total of 56 volunteers will be enrolled with 26 enrolling in part A and 30 in part B. For Part B, 20 volunteers (minimum 16) will be enrolled to receive FMP010 at 50 µg in AS01B (Group 3) and 10 (minimum 8) volunteers enrolled to receive a comparator rabies vaccine Rabipur (Group 4). This part will be randomized and blinded.

## 5.4 Safety considerations for the trial

A Safety Monitoring Committee (SMC) will be appointed to review the safety data from Part A (USA). The SMC will consist of a three experienced clinicians not already participating on the study team recommended by the PI and approved by the study partners. The primary responsibilities of the SMC are to review and evaluate the accumulated study data for participant safety after first vaccination of Group 1, after second vaccination of Group 2, and as needed if safety concerns should arise in other times during the trial, and make recommendations to the PI concerning the continuation, modification or termination of the study. It is not the role of the SMC to comment on the study design, conduct or interpretation, but rather to act as independent experts in evaluating adverse events. The SMC may, if deemed necessary, convene a meeting with, or request further information from the PI or the Medical Monitor.

### Procedure for Evaluating Vaccine Safety in Part A and Progression to Part B

Vaccination and review of the safety data for Groups 1 and 2 (Part A in the USA) will occur before vaccination can begin in Part B (Kisumu, Kenya). Safety data for Groups 1 and 2 (Part A in the USA) will be collected and submitted to a Safety Monitoring Committee (SMC) for recommendations about progression to Part B in Kisumu, Kenya. If progression to Part B is recommended the safety data will be presented to the Medical Monitor for Part B and the KEMRI Ethical Review Committee for evaluation and recommendation to initiate Part B of the study.

### Procedure for Evaluating Vaccine Safety in Part B and Progression to the Next Dose

The following Hold Rule will be used to determine if Part B of the study can progress to the second and third vaccination dose

### Holding Rule for Progression to Next Dose in Part B

- Vaccination with the next dose can be put on hold if five subjects develop a Grade 3 adverse event beginning within two days after vaccination, and persisting at Grade 3 for ≥ 72 hours if the adverse event is malaise, myalgia, fatigue, nausea, fever, headache, or joint pain.

Activation of the Holding Rule requires a thorough review by the Local Medical Monitor in Kenya (Part B, Kisumu, Kenya) and discussion between the investigators, the Medical Monitors, the safety monitoring committee, and Sponsor. Vaccination will restart only if all parties agree to a resumption of vaccination.

### Stopping Rules

The following Stopping Rules for individual subjects will apply (i.e., the withdrawal of an individual subject from further vaccination):

Stopping Rules:

A. Local Reactions: Investigator discretion

B. Systemic adverse events: Individual subjects will be withdrawn from further vaccination if they develop a Grade 3 adverse event beginning within two days after vaccination, and persisting at Grade 3 for ≥ 72 hours if the adverse event is malaise, myalgia, fatigue, fever, headache, or joint pain.

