### Solicited adverse events

Solicited symptoms are adverse events occurring within the seven days follow-up period after vaccination that are inquired about by the investigator or specified designee. Space on the source documents and CRF will be allocated for the recording of solicited symptoms. Table 4 lists the solicited local and general adverse events for the study.

Table 4: Solicited local and general adverse events

|  | **Adverse events** |
| --- | --- |
| **Local (injection site)** | Pain at the injection site |
|  | Swelling at the injection site |
|  | Erythema at the injection site |
| **General** | Fever* (Oral Temperature) |
|  | Gastrointestinal (Nausea) |
|  | Headache |
|  | Malaise |
|  | Myalgia |
|  | Fatigue |
|  | Joint pain |

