## Assessment of intensity

Intensity of the solicited adverse events should be assessed as described in Tables 5-7. Grading of hematological and biochemical laboratory adverse events are in Table 8-9.

Table 5: Intensity grading of local solicited adverse events

| **Adverse event** | **Intensity grade** | **Intensity** |
| --- | --- | --- |
| Pain at injection site | 0 | Absent |
|  | 1 | Mild pain not interfering with function |
|  | 2 | Moderate pain; pain interfering with function but not interfering with activities of daily living (ADL) |
|  | 3 | Severe Pain; pain that severely interferes with ADL |
| Erythema at injection site | | Record greatest surface diameter in mm (see Table 9 ) |
| Swelling at injection site | | Record greatest surface diameter in mm (see Table 9 ) |

Intensity of the general adverse events should be assessed as described in Table 8.

Table 6: Intensity grading of general solicited adverse events

| **Adverse event** | **Intensity grade** | **Intensity** |
| --- | --- | --- |
| Fever (oral temperature  37.5C or 99.5F). | | Record oral temperature in °C/F (see Table ) |
| Headache | 0 | Normal |
|  | 1 | Headache which is easily tolerated |
|  | 2 | Headache that interferes with normal activity |
|  | 3 | Headache that prevents normal activity |
| Fatigue | 0 | Normal |
|  | 1 | Fatigue which is easily tolerated |
|  | 2 | Fatigue that interferes with normal activity |
|  | 3 | Fatigue that prevents normal activity |
| Gastrointestinal | 0 | Normal |
| (*Nausea)* | 1 | GI symptoms which are easily tolerated |
|  | 2 | GI symptoms that interfere with normal activity |
|  | 3 | GI symptoms that prevent normal activity |
| Malaise | 0 | Normal |
|  | 1 | Malaise which is easily tolerated |
|  | 2 | Malaise that interferes with normal activity |
|  | 3 | Malaise that prevents normal activity |
| Myalgia | 0 | Normal |
|  | 1 | Myalgia which is easily tolerated |
|  | 2 | Myalgia that interferes with normal activity |
|  | 3 | Myalgia that prevents normal activity |
| Joint pain | 0 | Normal |
| (> 1 joint) | 1 | Joint pain which is easily tolerated |
|  | 2 | Joint pain that interferes with normal activity |
|  | 3 | Joint pain that prevents normal activity |

Table 7: Intensity grading assigned

| Erythema at injection site | 0 | 0 mm |
| --- | --- | --- |
|  | 1 | > 0 - 20 mm |
|  | 2 | > 20 - 50 mm |
|  | 3 | > 50 mm |
| Swelling at injection site | 0 | 0 mm |
|  | 1 | > 0 - 20 mm |
|  | 2 | > 20 - 50 mm |

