The investigator should not wait to receive additional information to fully document the event before notifying GlaxoSmithKline Biologicals, or the USAMRMC Office of Research Protection (MRMCORP) and the USAMMDA Product Manager of a serious adverse event. This initial notification should give as minimum, sufficient information to permit identification of:

- The reporter
- The subject initials, identification number, date of birth, gender and ethnicity
- Study test article
- Date of administration
- Adverse events (Date of onset, signs/symptoms and severity)
- Action taken
- Concomitant medications (dose, route, duration)

In the event of a death or a serious adverse event determined by the investigator to be related to vaccination, receipt of the fax must be confirmed by a telephone call. The fax report should be followed by a full written report using either the GSK Biologicals Serious Adverse Events form or the US FDA MedWatch form, detailing relevant aspects of the adverse events in question. It should include copies of relevant hospital case records, autopsy reports, and other documents where applicable.

In the event that a serious adverse events determined by the investigator to be related to vaccination are detected following any vaccination in any of the vaccine groups, no further vaccinations will be administered until a written report has been submitted to KEMRI, the WRAIR IRB, HSRRB, USAMMDA Product Manager, and the FDA, and the investigators have conferred with the GSK, and WRAIR and/or USAMRU-K Medical Monitors.

If an instance of congenital abnormality in offspring is brought to the attention of the investigator at any time after cessation of study vaccine AND is suspected by the investigator to be related to study vaccine, it should be reported to the Study Contacts for Serious Adverse Event Reporting.

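### The individual stopping rule leaves out nausea, which the group holding rule includes, so Grade 3 nausea is handled differently in the two rules however the clause is read

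*Protocol*

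**What the plan says.** All references are to the protocol.

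- **Holding Rule for Progression to Next Dose in Part B (section 5.4).** The next dose can be put on hold when five subjects have a Grade 3 event that starts within two days and stays at Grade 3 for 72 hours or more, "if the adverse event is malaise, myalgia, fatigue, nausea, fever, headache, or joint pain".
- **Stopping Rules, item B, systemic events (section 5.4).** An individual is withdrawn from further vaccination on the same grade, onset and persistence, "if the adverse event is malaise, myalgia, fatigue, fever, headache, or joint pain".
- **Stopping Rules, item A.** "Local Reactions: Investigator discretion".
- **Solicited events (section 8.1.2, Table 4).** Seven general events are solicited: fever, nausea, headache, malaise, myalgia, fatigue and joint pain.
- **Intensity (section 8.2, Table 6).** Nausea has its own Grade 3 definition: "GI symptoms that prevent normal activity".
- **Elimination criteria (section 4.4).** These are checked at each visit after the first vaccination and include a discretionary item: "Any other concern of the PI or other investigator that precludes volunteer involvement in the study".
- **Visits 3-6 (section 5.5).** After dose 1, a Grade 3 event must be notified to the principal investigator or another physician investigator.

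**The concern.** The two rules work as a pair. One protects the individual and the other protects the group, and both rest on the same definition of a worrying systemic reaction. One symptom appears in only one of them, with no explanation, although it is solicited and graded exactly like the others.

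The wording adds to the difficulty. The closing clause of each rule directly follows the 72-hour condition, so it can be read in two ways: as the list of events that count at all, or as the list of events for which 72 hours is required. The protocol does not say which is meant. At stake is whether a subject with Grade 3 nausea must be withdrawn. Two investigators could apply the same sentence to the same event and reach opposite answers, and this is a mandatory withdrawal rule for a vaccine whose first use in humans is this study.

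**Working it through.** The plan states no figure for this point, so the main check is a comparison of text. A short calculation then gives the size.

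**Step 1. Compare the lists.**

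| General event in Table 4 | Holding rule | Stopping rule B |
|---|---|---|
| Malaise | yes | yes |
| Myalgia | yes | yes |
| Fatigue | yes | yes |
| Nausea | yes | **no** |
| Fever | yes | yes |
| Headache | yes | yes |
| Joint pain | yes | yes |
| Total | 7 of 7 | 6 of 7 |

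The other six stand in the same order in both rules. Nothing is in the stopping rule that is not in the holding rule.

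**Step 2. Apply each reading to nausea.**

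| Grade 3 nausea, onset within two days | Holding rule | Stopping rule B |
|---|---|---|
| List defines which events qualify; lasts 72 h or more | counts toward the five | withdrawal not required |
| List defines which events qualify; lasts under 72 h | does not count | withdrawal not required |
| List limits only the 72 h condition; lasts 72 h or more | counts toward the five | withdrawal required |
| List limits only the 72 h condition; lasts under 72 h | does not count | withdrawal required |

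Under each reading there is one row where the two rules part company: row 1 under the first, row 4 under the second. For the other six symptoms the rules agree in every row.

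**Step 3. Look for a rule elsewhere that settles it.** The absolute contraindications in section 4.4.1 are pregnancy and "Acute allergic reaction, significant IgE-mediated event or anaphylactic shock following the administration of vaccine investigational product". Section 8.5.2 pauses dosing only for vaccine-related serious events: "no further vaccinations will be administered until a written report has been submitted". The elimination criteria in section 4.4 leave the decision to judgement. The notification duty at Visits 3-6 sends a Grade 3 event to a physician but does not say what to do about dosing. None of these is a mandatory rule for non-serious Grade 3 nausea.

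**Step 4. Ask whether frequency explains the omission.** In Table 1 (section 1.3.2), RTS,S/AS01B arm, gastrointestinal events of any grade followed 24 of 142 doses (16.9%) and arthralgia followed 24 of 142 (16.9%). Joint pain is in the stopping rule and nausea is not. Fever is also in the rule, although a footnote to Table 1 reports no Grade 3 fever. Expected frequency therefore does not explain the difference.

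**Step 5. Size.** Inputs: Grade 3 gastrointestinal events after 1 of 142 RTS,S/AS01B doses, 95% CI 0.0% to 3.9% (Table 1); 20 subjects with three doses each in Group 3.

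- FMP010 doses: 20 × 3 = 60
- Rate: 1/142 = 0.0070, or 0.7%
- Expected events: 60 × 1/142 = 0.42, or about 0.4
- At the CI limits: 60 × 0.000 = 0 and 60 × 0.039 = 2.3
- After doses 1 and 2 only, the doses after which withdrawal still prevents a vaccination: 40 × 1/142 = 0.28, or about 0.3

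These counts are for any duration. The documents do not give the share that lasts 72 hours.

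**The case against.** The best defence is that the rules differ in force and purpose. The holding rule is permissive and leads to a review by several parties; the stopping rule is mandatory for one person. Nothing says that the lists must match. Item B is also headed as covering systemic events generally, so reading the list as a limit on the 72-hour condition alone is natural. On that reading nausea is treated more strictly than the other six symptoms and no subject is under-protected. This stands as far as it goes, but it does not explain why nausea alone should be stricter in one rule and not in the other, and the protocol does not say that this reading is the right one.

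A reader might infer that the protocol forces, or plainly permits, unsafe redosing of a subject with severe nausea. The documents do not support that. On one reading the subject must be withdrawn. On the other, section 4.4 allows withdrawal for a medical condition that raises the subject's risk or for any other investigator concern, Grade 3 events at the post-dose-1 visits go to a physician, and section 4.4.1 defers dosing during moderate or severe acute illness. The Safety Monitoring Committee can also review data when concerns arise.

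A reader might also infer that the two rules contradict each other. They do not: both can be followed at once. Nor is local reactogenicity a gap in the individual rule, since item A leaves it to the investigator. No endpoint, estimate or analysis is shown to be affected.

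**Conclusion.** The inconsistency is real and minor. One of seven solicited general events is omitted from the individual rule without a reason, and the two rules treat it differently under either reading. What is missing is a single stated meaning for a mandatory rule; investigator discretion is present throughout.

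The expected burden is small: about 0.4 Grade 3 gastrointestinal events over 60 FMP010 doses, with 0 to 2.3 at the confidence limits. This assumes that a per-dose rate seen in malaria-naive adults with a different antigen in the same adjuvant carries over to Kenyan adults, and that the gastrointestinal category of Table 1 is close to nausea. Events lasting 72 hours can only be some part of that number. The textual finding does not depend on this calculation.

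**What to change.** 1. Add nausea to item B of the Stopping Rules, so that both rules name the same seven symptoms.
2. State in both rules that the 72-hour persistence applies to these seven symptoms, and that any other systemic Grade 3 event starting within two days counts whatever its duration.

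The first change alters an operative rule. If the list defines which events qualify, Grade 3 nausea lasting 72 hours would now require withdrawal. If it limits only the 72-hour condition, brief Grade 3 nausea would no longer require it. The second change removes the choice between readings; for anyone who has been using the list as a complete list of qualifying events, it widens both rules.

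The cost is one word and one sentence per rule in an amendment. No visit, procedure or data item is added.
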